### Sample size

Our primary research hypothesis is that with the treatment algorithm a better patients’ perception of symptoms, knee function and ability to participate in sports activities will be achieved compared to the current practice after 24 months (superiority study). Patients’ perception of symptoms, knee function and ability to participate in sports activities will be evaluated at multiple time points during 2 year follow-up, and will be expressed as change in IKDC score (subjective form) compared to baseline. The standard deviation (SD) of the IKDC after 24 months of follow-up has been reported to be 10,7. We aim to find a clinically relevant additional effect of the algorithm to usual care. Therefore, our hypothesis is that the potential additional effect size should be minimally 0.5 (6 points). For the intra cluster correlation (ICC) coefficient we used an ICC of 0.10 which is reported for hospital processes. Based on a difference of 6 points, SD of 10.7, an ICC of 0.10 (randomization on hospital level), a power of 90%, an α of 0.05, and 10 participating hospitals; 20 patients per hospital need to be included (200 patients in total). To accommodate a 10% dropout rate, 23 patients per hospital are required, resulting in a final sample of 230 patients (10 hospitals * 23 patients per hospital).

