**Methods:**

The ROTATE-trial is a multicenter, open-labeled cluster randomized controlled trial with superiority design. Randomization will take place on hospital level (*n* = 10). Patients must meet all the following criteria: aged 18 year or older, with a complete primary ACL rupture (confirmed by MRI and physical examination) and maximum of 6 weeks of non-operative treatment. Exclusion criteria consists of multi ligament trauma indicated for surgical intervention, presence of another disorder that affects the activity level of the lower limb, pregnancy, and insufficient command of the Dutch language. The intervention to be investigated will be an adjusted treatment decision strategy, including an advice from our treatment algorithm. Patient reported outcomes will be conducted at baseline, 3, 6, 12 and 24 months. Physical examination of the knee at baseline, 12 and 24 months. Primary outcome will be function of the knee measured by the International Knee Documentation Committee (IKDC) questionnaire. Secondary outcomes are, among others, the Tegner activity score, the Knee injury and Osteoarthritis Outcome Score (KOOS) and the 9-item Shared Decision Making Questionnaire (SDM-Q-9). Healthcare use, productivity and satisfaction with ((non-)operative) care are also measured by means of questionnaires. In total 230 patients will be included, resulting in 23 patients per hospital.

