### Study design

The ROTATE-trial is an open-labeled cluster randomized controlled trial with superiority design. It is a multicenter study performed in orthopedic departments of ten hospitals throughout the Netherlands. Of the ten hospitals one is an academic hospital, one a private clinic and eight are general hospitals. In all participating hospitals, the local responsible authorities approved the conduct of the study. The study protocol was approved by the Erasmus MC Ethics Committee and was registered in the Dutch Trial Registry. (Registration number: NL8637).

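### The stated 90% power does not follow from the plan's own inputs: ten hospitals of 20 at ICC 0.10 give about 64% (normal) or 53% (t, 8 df), and no cluster size reaches 90%

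*Protocol article*

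**What the plan says.** The Sample size section of the protocol article sets out a full calculation for the primary outcome, the IKDC score at 24 months. The spread is taken from earlier data: "The standard deviation (SD) of the IKDC after 24 months of follow-up has been reported to be 10,7". The clustering allowance is also given: "we used an ICC of 0.10 which is reported for hospital processes". The target is worded as "our hypothesis is that the potential additional effect size should be minimally 0.5 (6 points").

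The calculation is then stated as "Based on a difference of 6 points, SD of 10.7, an ICC of 0.10 (randomization on hospital level), a power of 90" per cent, completed by α 0.05 and ten participating hospitals. Its result is that "20 patients per hospital need to be included (200 patients in total"). A 10% dropout allowance raises this to 23 per hospital, and the abstract repeats the total: "In total 230 patients will be included, resulting in 23 patients per hospital".

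The Study design section confirms that ten is the total number of hospitals: "It is a multicenter study performed in orthopedic departments of ten hospitals throughout the Netherlands". The Randomization section makes the hospital the unit of randomization. The Data analysis section plans a linear mixed model with hospital as a random factor and baseline IKDC as a covariate. The sample size uses no baseline correlation.

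**The concern.** With only ten clusters and an ICC of 0.10, variation between hospitals dominates the standard error, and recruiting more patients within each hospital helps little. A requirement of just 20 patients per hospital for 90% power therefore looked too small.

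This calculation supports the primary superiority hypothesis, and the Dissemination section says the authors intend to bring the results into the Dutch guideline for ACL injuries. If power is well below 90%, a non-significant result may be read as coming from a trial that would very probably have found a 6-point benefit. Under the stated inputs, the chance of missing such a benefit is 36% to 47%, not 10%.

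**Working it through.** **Inputs from the Sample size section:** difference 6 points; SD 10.7; ICC 0.10; α 0.05; target power 90%; ten hospitals; m = 20 evaluable patients per hospital.

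**Assumptions, because the article does not state them:** five hospitals per arm (the most favourable split), a two-sided test, and 10.7 as the total SD.

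**1. Individually randomized requirement.** n per arm = 2 × (1.96 + 1.2816)² × 10.7² / 6² = 66.8.

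**2. Design effect.** 1 + (20 − 1) × 0.10 = 2.9. With 20 per hospital, the need is 66.8 × 2.9 ≈ 194 per arm, or 388 in total. The plan has 100 per arm, an effective 100 / 2.9 = 34.5.

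**3. Power of the plan.** SE = 10.7 × √(2 × 2.9 / 100) = 2.577, and 6 / 2.577 = 2.33.
- Normal: Φ(2.33 − 1.96) = 64.4%.
- Noncentral t with 10 − 2 = 8 df: 53.4%.

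**4. Ceiling.** As patients per hospital grow without limit, SE tends to 10.7 × √(2 × 0.10 / 5) = 2.14. Then 6 / 2.14 = 2.80, and power is 80.1% (normal) or 69.1% (t). By the normal formula, 90% needs more than 66.8 × 0.10 = 6.7 hospitals per arm, hence at least 7. With t it is at least 8 (90.9%, against 86.1% with 7). Five per arm has no solution.

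**5. Hospitals needed at 20 patients each.** Normal: 10 per arm (90.9%). With t: 11 per arm (90.7%; 10 per arm gives 87.6%).

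**6. Detectable difference at 90% power with 5 × 20 per arm.** Normal: (1.96 + 1.2816) × 2.577 = 8.35 points. With t, 8 df: 9.57 points.

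**7. Attempts to reproduce 90%.**

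| Variant | Normal | t |
|---|---|---|
| All 23 per hospital retained | 66.2% | 55.1% |
| One-sided α 0.05 | 75.3% | 68.5% |
| One-sided α 0.05, unlimited patients per hospital | 87.7% | 81.9% |
| SD 12 (so that 6 points = 0.5 SD) | 54.6% | 44.7% |
| 10 hospitals per arm × 20 (20 hospitals, 400 patients) | 90.9% | 87.6% |

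Two changes of input bring the stated result back under the normal formula. One is an ICC of about 0.026 (0.007 with t). The other is counting the ten hospitals per arm: m = 66.8 × 0.9 / (10 − 6.68) = 18.1, so 19 per hospital. The second may explain the figure, but that is an inference, and the article fixes ten as the total.

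**8. Sensitivity to the ICC (5 × 20 per arm).**

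| ICC | Normal | t |
|---|---|---|
| 0.01 | 95.3% | 88.8% |
| 0.02 | 92.2% | 83.9% |
| 0.03 | 88.6% | 79.1% |
| 0.05 | 81.0% | 70.2% |
| 0.10 | 64.4% | 53.4% |

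**9. Other steps.** The dropout step is right: 20 / 0.9 = 22.2, rounded up to 23. The standardized effect is loose: 6 / 10.7 = 0.56, while 0.5 × 10.7 = 5.35 points. At 5.35 points, power would be 54.6% (normal) or 44.7% (t).

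**The case against.** The strongest objection is that the primary model adjusts for baseline IKDC, so the real power may be higher than the unadjusted figure. That is true. If baseline explained 25% of the variance at both patient and hospital level, power would be about 77% (normal) or 66% (t). But the stated calculation uses the unadjusted SD and claims no such gain. Reaching 90% would need R² of about 0.48 (normal) or 0.61 (t), a correlation of roughly 0.7 to 0.8 (√0.48 = 0.69; √0.61 = 0.78). The article offers no figure to support that. What stands is that the 36% to 47% risk applies to the stated inputs and is not a forecast for the adjusted analysis.

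A second objection is that 53% rests on a choice of degrees of freedom that the article does not make and may leave to the SAP. This is fair, so both figures are given. The 64% is the direct check of a conventional formula and already contradicts 90%. Sidedness and the split between arms are likewise unstated, but a one-sided test stays below 90% at any cluster size, and an unequal split lowers power.

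Third, the 0.5 is worded as a minimum, which 0.56 satisfies, and the calculation itself uses 6 points and 10.7. That remark is a minor point of wording.

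Finally, nothing in the article says a null result would be read as no benefit. That is a risk created by the 90% claim, not a stated intention.

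**Conclusion.** The concern holds. The inputs and result are all printed in one section, and the result does not follow from them: about 64% power (normal) or 53% (t, 8 df) instead of 90%, with ceilings of 80% and 69% however many patients each hospital recruits. This rests on a 5:5 split, a two-sided test and 10.7 as the total SD. None of the alternative readings with ten hospitals and ICC 0.10 restores 90% without a baseline gain that the article does not claim. Real power could be materially better if the true ICC is well below 0.10 or baseline IKDC is strongly predictive, but the article would have to state and support this. Because the power for the primary hypothesis is misstated and only wording is needed to correct it, it must be fixed.

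**What to change.** In the Sample size section, and in the SAP if it repeats the claim:

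- Replace the 90% statement. With ten hospitals (five per arm), 20 evaluable patients each, ICC 0.10 and two-sided α 0.05, power for 6 points without baseline adjustment is about 53% (t, 8 df; 64% by the normal formula). The difference detectable with 90% power is about 9.6 points (8.4 by the normal formula).
- State the sidedness, the number of hospitals per arm and the degrees-of-freedom method.
- Show power over a range of ICC values, for example 0.01 to 0.10. If a documented ICC for a patient-reported outcome is smaller than the one for hospital processes, cite it and recompute. Do the same for any baseline correlation relied on.
- Check whether the ten hospitals were entered as a per-arm count.
- Give the standardized effect as 0.56, or the difference as 5.35 points if 0.5 SD is the real target.
- State that a non-significant result will be interpreted from the confidence interval against the 6-point difference, not as evidence of no benefit.

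The cost is wording and a less favourable power figure. No additional hospitals, patients or changes to conduct are needed. The fix makes the power statement honest; it does not raise the power.

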### Data analysis

#### Primary outcome

In our primary analysis patients will be analysed according to their randomization group. To answer our primary research question, we will use linear mixed models to evaluate the between group difference in patients’ outcome as assessed by the IKDC questionnaire. The IKDC score after 24 months follow-up will be used as dependent variable. The randomized allocation will be used as an independent variable. We will adjust the analysis for potential confounders, namely baseline IKDC score. The used cluster (hospital) will be added as random factor into the model. The following model assumptions will be checked: linearity, homoscedasticity and normality of residuals.

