### Secondary outcomes

At baseline we will collect the following baseline characteristics, age, sex, height, weight, educational level, smoking habit, side affected and date and kinetics of trauma. Patient-rated outcome measures (PROMs) will be sent online at baseline, 3, 6, 12 and 24 months. There is an overview of all PROMs per follow-up moment in Table 1.

**Table 1 Tab1:** Patient-rated outcome measures (PROM) per follow-up moment

*PROMs*	*Baseline/1st consult*	*3 months*	*6 months*	*12 months*	*24 months*
*IKDC - subjective*	*x*	*x*	*x*	*x*	*x*
*Tegner*	*x*	*x*	*x*	*x*	*x*
*KOOS*	*x*				*x*
*Lysholm*	*x*	*x*	*x*	*x*	*x*
*NRS*	*x*	*x*	*x*	*x*	*x*
*Tampa scale*	*x*			*x*	*x*
*EQ-5D-5L*	*x*	*x*	*x*	*x*	*x*
*SDM-Q-9*	*x*				
*iMCQ/iPCQ*		*x*	*x*	*x*	*x*

*PROM* patient-rated outcome measures, *IKDC* International Knee Documentation Committee, *KOOS* Knee injury and Osteoarthritis Outcome Score, *NRS* number rating scale, *EQ-5D-5L* EuroQol 5D, *SDM-Q-9* 9-ltem Shared Decision Making Questionnaire, *iMCQ* Medical

We will measure the patients’ perception of symptoms, knee function and ability to participate in sports activities at 3, 6 and 12 months follow-up with the IKDC questionnaire. As mentioned above, the 24 month follow-up will be our primary outcome. Work and sports activities will be measured with the Tegner questionnaire (range 0–10; highest activity score is 10) at baseline, 3, 6, 12 and 24 months [12]. The Knee injury and Osteoarthritis Outcome Score (KOOS) will be assessed at baseline and 24 months of the subscales pain, symptoms, ADL, sports and quality of life (QoL) (range 0–100; optimal score is 100) [13]. Knee instability will be measured with the Lysholm questionnaire (range 0–100; optimal score is 100) at baseline, 3, 6, 12 and 24 months [12]. Knee pain will be assessed with the number rating scale (NRS) (range 0–10; optimal score is 0) at baseline, 3, 6, 12 and 24 months. Kinesiophobia will be measured with the Tampa scale at baseline (range 17–68; optimal score is 17), 12 and 24 months [14]. General quality of life will be measured with the EQ-5D-5L questionnaire (range − 0.329 to 1; optimal score is 1) at baseline, 3, 6, 12 and 24 months. EQ-5D-5L use is recommended for the assessment of quality of life in trauma patients, especially for economic assessments. The patients’ EQ-5D-5L health states will be converted into utility scores using the Dutch tariff. The EQ-5D will be used for the cost-utility analysis [15].

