#### Secondary outcome

To evaluate the between group difference in course in IKDC scores over the follow-up period, as indicated by the interaction between time point and randomized allocation, we will use mixed models. The IKDC score (at baseline and after 3, 6, 12 and 24 months of follow-up) will be used as a dependent variable. The randomized allocation will be used as an independent variable. Follow-up period and the interaction between follow-up and randomized allocation will be entered into the model as fixed factors.

Difference between groups in knee pain, kinesiophobia, shared decision making for patients and quality of life will be used as secondary outcomes. The analyses will be performed by using linear or binary mixed models for repeated measures. Return to pre-injury sport level, satisfaction with treatment and adverse events will be reported as comparative frequencies. Because of the potential for type 1 error due to multiple comparisons, findings for analyses of secondary endpoints should be interpreted as exploratory.

Difference between groups in shared decision making for physicians will be analyzed qualitatively, using the transcripts of the interviews’/focus groups’ audio files. The coding process will result in themes and patterns of shared meaning, underpinned or united by a central concept which are important for our research question [19].

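### As written, the primary model draws only on the 24-month IKDC and ignores the 3-, 6- and 12-month scores, leaving it exposed to bias of about 0.4 to 1.2 points if recovery-related dropout differs by arm

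*Protocol article*

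**What the plan says.** All references are to the protocol article.

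- **Data analysis, Primary outcome.** The model is fixed element by element. The response: "The IKDC score after 24 months follow-up will be used as dependent variable". The covariate: "We will adjust the analysis for potential confounders, namely baseline IKDC score". The random effect: "The used cluster (hospital) will be added as random factor into the model". Allocation is the remaining predictor. No patient-level effect and no interim visit appears. On the analysis set: "In our primary analysis patients will be analysed according to their randomization group".
- **Secondary outcomes and Table 1.** The questionnaire is also completed between baseline and the end of follow-up: "ability to participate in sports activities at 3, 6 and 12 months follow-up with the IKDC questionnaire".
- **Data analysis, Secondary outcome.** The course of IKDC gets its own model: "The IKDC score (at baseline and after 3, 6, 12 and 24 months of follow-up) will be used as a dependent variable". It includes an allocation-by-follow-up interaction, and findings on secondary endpoints are to be read as exploratory.
- **Sample size.** Loss is expected: "To accommodate a 10% dropout rate, 23 patients per hospital are required". The target difference is 6 points with an SD of 10.7.

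The article does not say what happens to a patient whose 24-month score is missing.

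**The concern.** A linear mixed model is often credited with coping well with dropout. That protection comes from repeated measurements within patients: the earlier scores carry information about the missing one. The primary model here has one response per patient, and its only random effect is hospital. A patient lost after month 12 therefore contributes nothing when the model is fitted as stated, although up to three follow-up scores are on file.

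What is at stake is bias in the confirmatory estimate. Enlarging the sample from 20 to 23 per hospital replaces the number lost but does nothing about who is lost. The trial is open-label and its outcome is patient-reported. The Objectives expect the arms to differ in surgery rate, delayed surgery and speed of recovery. It is plausible, though not shown, that patients doing well or badly stop answering at different rates in the two arms. The interim scores that would correct for this are already planned, yet they serve only the exploratory analysis.

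**Working it through.** **Inputs from the article:** target difference 6 points; SD 10.7; ICC 0.10; 10 hospitals; 20 patients per hospital before and 23 after a 10% dropout allowance.

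**Assumed, because the article gives no figure:** five hospitals per arm; correlation of 12- with 24-month IKDC 0.5 to 0.7; correlation of baseline with each later score 0.3; the dropout patterns below.

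**1. The plan's dropout step.** 20 / (1 − 0.10) = 22.2, rounded up to 23 per hospital and 230 in total. This reproduces. Expected with a 24-month score: 230 × 0.90 = 207. Expected without: 23.

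**2. Order of magnitude.** If only one arm has selective loss, the bias in its mean is the dropout share × the gap between completers and dropouts. With 10% and assumed gaps of 0.5 and 1 SD:
- 0.10 × 5.35 = 0.54 points
- 0.10 × 10.7 = 1.07 points

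**3. Simulation with baseline adjustment.** Baseline, 12- and 24-month scores were generated for a very large sample with SD 10.7, a true difference of 6 and no clustering. Dropout followed a logistic model in the 12-month score within arm, with a slope of 1 on the log-odds scale per SD where selective. Two analyses were compared: the 24-month model on completers, and the same model after predicting missing 24-month scores from baseline and 12-month IKDC within arm.

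| Dropout, control / algorithm arm | Relation to 12-month score | Bias, completers (correlation 0.5 / 0.7) | Estimate using 12-month score |
|---|---|---|---|
| 10% / 10% | none | −0.02 / −0.01 | 5.98 / 5.99 |
| 10% / 10% | poorer scorers leave, both arms | −0.02 / −0.04 | 5.99 / 5.97 |
| 5% / 15% | none | 0.01 / 0.00 | 6.01 / 6.00 |
| 5% / 15% | poorer scorers leave, both arms | 0.36 / 0.58 | 5.97 / 6.02 |
| 10% / 10% | poorer leave in algorithm arm only | 0.41 / 0.58 | 6.01 / 5.99 |
| 10% / 10% | better leave in control, poorer in algorithm arm | 0.83 / 1.21 | 6.02 / 6.02 |

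Simulation error is a few hundredths of a point. Swapping the arms reverses the sign. Unequal rates alone do no harm, and nor does selective loss that is the same in rate and pattern in both arms. Where selective loss differs between arms, the range is about 0.4 to 1.2 points: 0.4 / 6 = 7% to 1.2 / 6 = 20% of the target.

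**4. Precision.** SE = √[(2/5) × (0.10 × 10.7² + 0.90 × 10.7² / m)], with m the effective number per hospital.
- Completers only, m = 23 × 0.90 = 20.7: SE = √[0.4 × (11.449 + 4.978)] = 2.56; power 64.8% (two-sided 5%, normal approximation).
- Recovering a share r² of the 2.3 lost per hospital, r = 0.5 to 0.8: m = 21.3 to 22.2; SE = 2.55 to 2.54; power 65.2% to 65.7%.

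Between-hospital variance dominates, so the interim scores add almost nothing to power. That these figures fall short of the stated 90% is a separate matter and has no bearing here.

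**The case against.** The strongest reply is that the article is silent on missing data, that such handling is commonly left to an analysis plan or full protocol not shown here, and that imputing 24-month IKDC from the interim scores and then fitting exactly the stated model would fit every word of the text. This stands. A reader might infer that the plan commits to a complete-case analysis and drops every patient who misses month 24; the document does not support that. What remains reviewable is the choice it does state: a primary model that by itself cannot use the interim scores.

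Second, a baseline-adjusted 24-month model answers the primary objective directly, and the secondary objective on the course of recovery has its own model. That also stands: objectives and models match. The point is robustness to dropout, not a wrong target.

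Three further inferences are tempting and should not be drawn:
- That the analysis breaks its own as-randomised principle. The sentence says in which arm a patient is analysed; it does not promise an outcome for everyone.
- That information is lost in a way that matters for power. The precision check shows almost no gain from using all visits.
- That unequal dropout is itself a bias. It is not, and even the completer analysis allows missingness to depend on allocation and baseline IKDC.

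Finally, the dropout patterns are assumptions, and nothing in the article shows that dropout will relate to recovery differently by arm. This is correct and limits the conclusion to a conditional one.

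**Conclusion.** The point holds in a limited form. Fitted as stated and without imputation, the primary model takes nothing from the roughly 10% of patients expected to lack a 24-month score, and it leaves unused the interim IKDC scores that the secondary model already employs. Its estimate is protected when missingness depends on no more than allocation and baseline IKDC, or acts alike in both arms. Otherwise the bias is about 0.4 to 1.2 points, 7 to 20% of the 6-point target, in either direction. That range rests on 10% average dropout, a 12-to-24-month correlation of 0.5 to 0.7, and selection on the 12-month score that differs between arms in pattern or extent. The consequence is exposure to bias, not loss of power. It is a worthwhile improvement to a stated choice, not a contradiction in the plan.

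**What to change.** Take the primary 24-month between-arm contrast from one repeated-measures mixed model of IKDC at 3, 6, 12 and 24 months. It should contain allocation by categorical time, baseline IKDC (with its interaction with time), correlation within patients, and a hospital random effect. Add a hospital-by-time effect only if ten hospitals allow it to be estimated.

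An equivalent route keeps the stated model and says that missing 24-month scores are imputed beforehand from the 3-, 6- and 12-month scores.

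In either case, keep the 24-month-only baseline-adjusted analysis as a sensitivity analysis.

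The cost is a change of wording and a slightly more complex model; no new data are needed. The result relies on missing at random given the observed scores. That is weaker than dependence on allocation and baseline alone, but it still does not cover dropout driven by what happens after the last completed questionnaire.

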### Recruitment procedures

All adults with an ACL rupture, visiting an orthopedic surgeon of one of the participating hospitals, who meet the eligibility criteria will be invited to participate. These patients receive the participant information sheet and will have sufficient amount of time to decide upon participation. Written informed consent is obtained from the patient prior to inclusion. At inclusion, the patient and physician will come to a treatment preference dependent on which treatment decision strategy they will use.

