### Randomization

To avoid dilution between both treatment decision strategies, randomization will take place on hospital level. This means that the treatment choice of all patients referred by one hospital will be based on the same treatment decision strategy. This will be done to overcome that the treatment choice of a participating orthopedic surgeon is influenced by knowledge of the algorithm, in case the patient is assigned to the control group. Secondly, this will be done to overcome logistic difficulties such as switching back and forth between different treatment decision strategies. Randomization will take place when institutional review board acceptance has been obtained, and will be executed by the use of a computer generated randomization list.

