Intramural and extramural medical costs will be assessed with the Medical Consumption Questionnaire (iMCQ) and productivity loss will be assessed with the Production Consumption Questionnaire (iPCQ) at 3, 6, 12, and 24 months follow-up. These questionnaires are validated by the Institute of Medical Technology Assessment (Erasmus University, Rotterdam, The Netherlands). iMCQ includes details on medical specialist care, physical therapy, hospitalization, nursing home, home care, and other costs directly associated with diagnosis, treatment and rehabilitation. iPCQ includes details on work resumption and production losses [16].

For patients, the efficacy of the shared decision making process will be evaluated using the score on the 9-ltem Shared Decision Making Questionnaire (SDM-Q-9) that is administered directly after the consultation. The SDM-Q-9 is a patient-reported measure that focuses on the decisional process by rating physicians’ and patients’ behavior in medical encounters [17]. The aggregated scores over all items of the SMD-Q-9 lead to a total raw score between 0 and 45, with 0 indicating the lowest and 45 indicating the highest level of perceived shared decision making.

For physicians, the efficacy of the shared decision making process will be evaluated at one or two time points, at the start of the inclusion period prior to the first inclusion in intervention and control centers and at the end of the inclusion period after the last inclusion in intervention centers. This will be evaluated using interviews/focus groups. The proposed topic lists are based on the SDM-Q-9-Doc questionnaire (the physician version of the SDM-Q-9) and the Technology Acceptance Model (TAM) [18]. Every interview/focus group session will be analyzed qualitatively and compared between control and intervention centers. After the inclusion period, we will analyze whether there is an improvement of perceived shared decision making when using our treatment algorithm.

Physical examination of the knee will be assessed by the objective IKDC questionnaire at baseline, 12 and 24 months. (Table 2) Information about the received treatment is reported including the surgeons fidelity to the intervention. We address the number of patients that cross over from their allocated treatment. (Serious) Adverse events ((S)AE’s) are noted.

**Table 2 Tab2:** Measurements per follow up moment

	*Baseline*	*3 months*	*6 months*	*12 months*	*24 months*
*Physical examination*	*x*			*x*	*x*

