## Discussion

This study is a cluster randomized trial and therefore can be susceptible to selection bias [24]. In order to minimize this risk independent treating physicians are recruiting participants for this study. Because every physician from both intervention and control hospitals have been exposed to the same amount of trial training, the potential for selection bias is reduced.

This study is an open-label trial. The intervention to be investigated is visually different for the patient and treating physician. Randomization status will therefore not be blinded.

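### Unblinded physicians recruit patients after hospitals are randomised, yet the primary model adjusts for baseline IKDC alone and equal training is offered as protection against selection bias

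*Protocol article*

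**What the plan says.** **Order of events.** The Randomization section makes the hospital the unit ("To avoid dilution between both treatment decision strategies, randomization will take place on hospital level") and ties the timing to ethics approval: "Randomization will take place when institutional review board acceptance has been obtained". Patients come later. Under Recruitment procedures, "At inclusion, the patient and physician will come to a treatment preference dependent on which treatment decision strategy they will use", so the hospital's strategy is in force when the patient enters. Under Secondary outcomes, the physician interviews in both types of centre are set "at the start of the inclusion period prior to the first inclusion in intervention and control centers".

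**Who recruits, and with what knowledge.** The Discussion admits that a cluster trial can suffer selection bias and answers: "In order to minimize this risk independent treating physicians are recruiting participants for this study". It adds that physicians in both arms had equal trial training and concludes that the potential for bias is reduced. It then says of the open-label design: "Randomization status will therefore not be blinded". Recruitment procedures also says that all eligible adults with an ACL rupture seen at a participating hospital will be invited.

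**The model.** Under Data analysis, Primary outcome, the linear mixed model has 24-month IKDC as the dependent variable, allocation as the independent variable and hospital as a random factor. On covariates it says: "We will adjust the analysis for potential confounders, namely baseline IKDC score".

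**What is collected.** The baseline list under Secondary outcomes is "age, sex, height, weight, educational level, smoking habit, side affected and date and kinetics of trauma". Table 1 adds baseline Tegner, among other scores.

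**The concern.** When clusters are randomised before patients are identified, randomisation balances hospitals but not the choice of patients within them. A recruiter who knows the arm knows what the patient will be offered, and so may the patient. Who is approached, and who agrees, can then differ by arm.

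The protocol itself suggests a route. The Background names an active sporting career as a reason for operative treatment. The Objectives expect fewer reconstructions under the algorithm. Active patients who want surgery could therefore enter the two arms at different rates.

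The stated protections do not deal with this. Training given equally in both arms may make the eligibility criteria be applied more alike, but it leaves every recruiter aware of the arm. The protocol does not explain in what sense a treating physician is independent, when that physician also shares in the treatment decision.

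The word 'namely' in the model description fixes one confounder rather than leaving the list open. A systematic difference between arms in age, activity level or time since injury would then be corrected only as far as baseline IKDC carries it.

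**Working it through.** **1. Is the sequence established?** Ethics approval triggers the randomisation of hospitals; the strategy is in use at patient inclusion; interviews in both types of centre precede the first inclusion; status is not blinded. Together these place allocation, and the recruiter's knowledge of it, before recruitment. No statement points the other way.

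**2. Standard error implied by the protocol's inputs.** From Sample size: difference 6, SD 10.7, ICC 0.10, 10 hospitals with 20 evaluable patients each. Assumed: 5 hospitals per arm (no ratio is given) and a two-sided 5% test.

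SE = 10.7 × sqrt[(2/5) × (0.10 + 0.90/20)] = 10.7 × 0.241 = 2.58 points.

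Power for 6 points is 53% (t, 8 df) or 64% (normal). The protocol's 90% does not reproduce with 10 hospitals in total: 66.8 per arm × design effect 2.9 × 2 arms = 388 patients, against 200 planned. That is a separate matter; 53% serves here only as the baseline for step 5. The dropout step does reproduce: 20/0.90 = 22.2, rounded up to 23 per hospital.

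**3. Illustration of recruitment bias.** Assumed, not in the documents: partial correlation r between the omitted factor and 24-month IKDC given baseline IKDC, and a systematic difference s between arms in SD units of that factor.

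Bias = r × s × 10.7.

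| r | s | Bias (points) | Share of 6 points | Two-sided type I error (t, 8 df) |
|---|---|---|---|---|
| 0.1 | 0.1 | 0.11 | 2% | 0.050 |
| 0.2 | 0.3 | 0.64 | 11% | 0.056 |
| 0.3 | 0.3 | 0.96 | 16% | 0.063 |
| 0.3 | 0.5 | 1.60 | 27% | 0.086 |

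**4. Chance imbalance, kept apart.** The SD of a standardised covariate difference between arms is sqrt[(2/5) × (ICC + (1 − ICC)/20)]: 0.14 at covariate ICC 0 and 0.24 at 0.10. The covariate ICC is an assumption, because the protocol's 0.10 refers to hospital processes. The effect of such imbalance on the estimate is part of the 2.58-point SE in step 2, so it is not an addition to the bias in step 3.

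**5. Precision gain.** Assume that the added covariates explain 10% of variance.

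- If they reduce between- and within-hospital variance alike (0.10 to 0.09 and 0.90 to 0.81), SE = 2.44 and power = 58% (t, 8 df).
- If they reduce only within-hospital variance (0.90 to 0.80), SE = 2.53 and power = 55%.

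**The case against.** Adjusting for the baseline value of the outcome, with a random hospital effect, is a recognised and parsimonious primary model. The protocol describes IKDC as covering symptoms, function and sports ability, and as valid and responsive in ACL rupture, so baseline IKDC will remove part of any imbalance. The documents do not call the omitted variables prognostic. The rule to invite all eligible adults directly restricts the physician's discretion. The Discussion admits the risk and claims only that it is reduced. All of this stands and limits the weight of the point.

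It does not remove the point. The invitation rule does not govern consent, nor does it guarantee that every eligible patient is in fact approached. Training does not affect knowledge of the arm. The trial's own premise is that patient-specific information helps to predict who will respond to exercise, which makes it reasonable to consider more than one baseline factor.

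A reader might infer more in four ways, none of which the documents support:

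- That chance imbalance among ten hospitals biases the result. It does not; it is carried by the standard error.
- That baseline IKDC reflects little beyond acute symptoms. The protocol does not say this.
- That the lack of a screening log, or of adjustment of QALYs for baseline EQ-5D, is a fault. A condensed article may leave both to the full protocol or analysis plan.
- That recruitment bias is shown to exist. It is only possible.

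**Conclusion.** The point holds as a modest, inexpensive improvement to a model that the protocol has fixed. Allocation precedes recruitment, recruiters know the arm, equal training does not conceal it, and a single covariate is named although others are collected.

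The size of any bias cannot be derived from the documents. The range of about 0.1 to 1.6 points (2% to 27% of the target difference) rests wholly on the assumed correlations and arm differences, and its upper end needs both at their maximum. The gain in power is small, from about 53% to between 55% and 58%, given 5 hospitals per arm and 10% of variance explained. The case for the change therefore rests on protection against measured imbalance, with precision secondary. Adjustment cannot correct selection on factors that are not measured.

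**What to change.** 1. **Primary model.** Before analysis, pre-specify a small set of already collected patient-level covariates in addition to baseline IKDC, for example age, sex, baseline Tegner and time from trauma to baseline (from the recorded trauma date). Keep hospital as the random factor. Replace the wording that limits confounders to baseline IKDC.

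2. **Discussion.** Keep the admission that selection bias is possible. Stop presenting equal training as protection against recruitment bias. Refer instead to the rule that all eligible patients are invited and to the covariate adjustment, and say that adjustment handles measured imbalance only.

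The cost is wording and a few patient-level degrees of freedom out of about 200 evaluable patients. Patient-level covariates use no hospital-level degrees of freedom, and no new data collection is needed. Unmeasured selection remains and should be stated as a limitation.
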